### Randomization

Randomization will take place after the baseline assessment and before the intervention begins. The UC arm is chosen as the control condition because it meets ethical and moral requirements to attempt treatment. Eligible patients will be randomized to one of the two conditions using a stratified urn randomization procedure to increase the likelihood of balanced allocation of prognostic variables at baseline. We will stratify by two factors: (i) single/multiple tablet regimen, and (ii) detectable/undetectable viral load at baseline through a 2 × 2 factorial stratification, to assign them into intervention arm or UC arm within each of the four cells. Randomization is implemented electronically through REDCap.

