### Sample size calculation

Sample size calculation and power analysis were conducted based on the primary and secondary end points. For Aim 1, 55 subjects to be recruited in the ISS-SBDOH arm and 55 in the UC arm enable us to obtain stable point estimates and test the hypotheses for acceptability of the intervention program using one sample binomial approach. For the frequency and timeliness of SBDOH intervention and level of challenges, group sample sizes of 55 in the ISS-SBDOH arm and 55 in the UC arm will enable us to detect a difference as small as 0.5 in a continuous outcome (a medium Cohen’s effect size) with 80% power, and a significance level of 0.05 using a two-sided two-sample t-test. For Aim 2, using repeated measures analysis with intra-subject correlation of 0.1, a type I error of 0.05, a type II error of 0.2 (or 80% power), and average number of available data points 3.5, out of 5 data points (baseline, weeks 4, 8, 12, 16), 55 subjects in each of the two arms will enable us to detect a difference as small as 0.29 in standardized unit of the outcomes (e.g., adherence to ART) between the two arms, which is statistically and clinically meaningful. For Aim 3, for the binary outcome variable of viral suppression, using repeated measures analysis with similar set-up as Aim 2, the sample size of 55 participants in each of the 2 arms will be able to detect a 9% difference (or an odds ratio of 2.7) between the 2 arms (assuming 85% viral suppression at week 16 for control arm) and this effect size is considered clinically meaningful. Thus, the planned sample size should be sufficient for the proposed analyses.

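### The Aim 2 detectable difference of 0.29 SD rests on one very low intra-subject correlation (0.1), and 55 per arm does not reach it at that value or at higher ones

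*Protocol article*

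**What the plan says.** In the protocol article, Sample size calculation, the Aim 2 figure is obtained "using repeated measures analysis with intra-subject correlation of 0.1", with "a type I error of 0.05", 80% power and "average number of available data points 3.5, out of 5 data points (baseline, weeks 4, 8, 12, 16"). With 55 per arm it states a detectable difference of 0.29 in standardized units. Sidedness is given only for the Aim 1 calculation ("using a two-sided two-sample t-test").

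For viral suppression in Aim 3 the inputs are carried over, "using repeated measures analysis with similar set-up as Aim 2", and lead to a 9-point detectable difference (odds ratio 2.7) from 85% in the control arm. The section then concludes that the planned number is enough.

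Two other sections bear on this:

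- **Tests.** Under Aim 2, an arm indicator tests whether the level of adherence differs between arms across the contact periods. Under Aim 3, the stated test is an arm-by-time interaction with baseline among the visits.
- **Randomization.** The article uses a "stratified urn randomization procedure to increase the likelihood of balanced allocation of prognostic variables at baseline", and adds: "We will stratify by two factors: (i) single/multiple tablet regimen, and (ii) detectable/undetectable viral load at baseline".

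**The concern.** When arm averages over several visits are compared, the intra-subject correlation decides how much information repeat visits add. A value of 0.1 says that two measurements on one patient, taken weeks apart, are almost unrelated. That makes each extra visit worth much more than it would be if patients differed stably from one another.

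Other parts of the design lean towards stable differences. Randomization is balanced on baseline viral load as a prognostic factor, and eligibility includes lasting circumstances such as unstable housing, substance use disorder and poverty.

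Adherence is a primary outcome. If the detectable difference is understated, a null adherence result could be read as evidence of no effect when the trial had limited power to see the effect it named.

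**Working it through.** **Inputs.** n = 55 per arm, m = 3.5 points on average, correlation r = 0.1, alpha 0.05, power 80%, all from Sample size calculation. Two-sided alpha is an assumption for Aim 2, taken from the Aim 1 wording. The article gives no other value of r, so 0.3, 0.5 and 0.7 are assumptions.

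**What r = 0.1 means.** One visit explains 0.1² = 1% of the variance of another. For suppression at 85%:

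- P(suppressed | suppressed at another visit) = 0.85 + 0.1 × 0.15 = 86.5%
- P(suppressed | unsuppressed at another visit) = 0.85 × 0.9 = 76.5%

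**Reproducing the Aim 2 figure.** For a difference in arm averages with equal correlation between visits, SE² = (2/55) × (1 + 2.5r)/3.5. The detectable difference is (1.96 + 0.84) × SE, and power for 0.29 is Φ(0.29/SE − 1.96).

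At r = 0.1: SE² = 0.03636 × 1.25/3.5 = 0.01299 and SE = 0.1140. The detectable difference is 0.32 SD, not 0.29. Power for 0.29 is Φ(2.54 − 1.96) = 72%. About 67 per arm would be needed for 0.29.

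A value near 0.29 appears only with other inputs: all 5 points (0.283), one-sided alpha (0.283), a first-order autoregressive correlation with 4 points (0.288), or r of about 0.01.

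**Varying r (Aim 2, arm averages).**

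| r | SE | Detectable difference (SD) | Power for 0.29 SD | n per arm for 0.29 SD |
|---|---|---|---|---|
| 0.1 | 0.114 | 0.32 | 72% | 67 |
| 0.3 | 0.135 | 0.38 | 58% | 94 |
| 0.5 | 0.153 | 0.43 | 47% | 120 |
| 0.7 | 0.169 | 0.47 | 40% | 147 |

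The drop from 80% to 72% is arithmetic at the article's own r. Only the further drop from 72% is due to r.

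**Baseline as covariate.** If baseline is always observed, 3.5 points leave 2.5 after baseline. The variance factor (1 + 2.5r)/3.5 is replaced by (1 + 1.5r)/2.5 − r². This gives 0.45, 0.49, 0.45 and 0.33 at r = 0.1, 0.3, 0.5 and 0.7, and detectable differences of 0.36, 0.37, 0.36 and 0.31 SD.

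**Aim 3, arm averages.** SE² = [(0.85 × 0.15 + 0.94 × 0.06)/55] × (1 + 2.5r)/3.5. Power for 85% versus 94% is 74%, 60%, 49% and 42% at the same four values of r. A pooled variance gives about one point less each time.

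**Aim 3, the planned test.** For a linear arm-by-time effect, approximated on a standardized outcome with five complete points, the SE of the slope difference per visit interval is √[2(1 − r)/(55 × 10)]. The detectable divergence over 16 weeks (four intervals) is 2.80 × 4 × SE: 0.64, 0.57, 0.48 and 0.37 SD at r = 0.1, 0.3, 0.5 and 0.7. Here a higher r helps.

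**The case against.** Four points can be made for the plan.

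- **The stratifier is no contradiction.** A reader might infer that stratifying on baseline viral load refutes r = 0.1. It does not. At r = 0.1 baseline status still separates 86.5% from 76.5%, a 10-point gap that is larger than the 9-point target effect. The Randomization section claims no particular strength of prognosis. The argument also bears on adherence only indirectly. This stands: it is a tension.
- **Low correlation in adherence is not absurd.** Self-report covers seven days, some eligibility criteria describe recent states, and the trigger of three missed days in five presumes episodic lapses. This stands as a reason not to assert a particular r. It does not bring 0.29 within reach, because 0.29 is missed even at 0.1.
- **The result depends on the model.** The Aim 2 text does not say how baseline enters. Adjusting for baseline with 3.5 post-baseline points would give 0.29 SD at r of about 0.7. However, the calculation counts baseline among its five points, so that is not what it describes.
- **The article gives no source for 0.1.** That is ordinary in a condensed article and is not the criticism. The printed value and the figure derived from it are.

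A reader might also infer that the low r overstates power for Aim 3 as planned. The documents do not support that: for the arm-by-time test the direction is reversed.

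**Conclusion.** The stated 0.29 SD at 80% power is not delivered by 55 per arm under the article's own inputs with a two-sided test, and the single value r = 0.1 is the favourable end for that comparison. The detectable difference is 0.32 SD at r = 0.1 and 0.38 to 0.47 SD at r from 0.3 to 0.7, or about 0.31 to 0.37 SD over that range with baseline as a covariate and 2.5 post-baseline points.

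This rests on two-sided 0.05, equal correlation between visits, and an assumed range for r. It does not show that true power is 40% to 58%, because the documents do not give the true correlation.

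For Aim 3, the 9-point figure belongs to an arm-average comparison, and even there power is about 74% at r = 0.1. It does not describe the planned interaction test.

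**What to change.** In Sample size calculation:

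1. Restate the Aim 2 detectable difference over a range of correlations (for example 0.1, 0.3, 0.5 and 0.7), or at the value observed in the team's earlier ingestible sensor study. State the sidedness.
2. Say whether baseline is an outcome point or a covariate, and count the available points accordingly.
3. For Aim 3, state that the 9-point figure applies only to a comparison of arm averages, with its power by correlation, and recompute the detectable effect for the arm-by-time test.
4. Reword the conclusion that the sample size is enough to match the restated figures.

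The cost is a rewritten paragraph and less favourable stated figures. Enrolment and trial conduct do not change.

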### Statistical analyses

We will use α < 0.05 as the significance level for statistical testing, and will use appropriate corrections (e.g., Bonferroni correction) for multiple comparisons to ensure that the effective type I error remains at 0.05 level. Statistical analyses will be conducted on an intention-to-treat sample using the SAS and R statistical software.

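### At two-sided 0.05 with exchangeable correlation, the stated inputs give 0.32 SD (Aim 2) and 9.6 points (Aim 3), not the printed 0.29 SD and 9 points

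*Protocol article*

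**What the plan says.** All the inputs stand in one paragraph, Sample size calculation. For Aim 2 the calculation is made "using repeated measures analysis with intra-subject correlation of 0.1", with "a type I error of 0.05, a type II error of 0.2 (or 80% power"), an "average number of available data points 3.5, out of 5 data points (baseline, weeks 4, 8, 12, 16"), and "55 subjects in each of the two arms". The stated result is that the trial can "detect a difference as small as 0.29 in standardized unit of the outcomes".

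For Aim 3 the outcome is viral suppression, with 85% assumed in the control arm at week 16. The set-up is described as similar to Aim 2, and the sample "will be able to detect a 9% difference (or an odds ratio of 2.7) between the 2 arms".

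Sidedness is given once, for the Aim 1 comparison: "a significance level of 0.05 using a two-sided two-sample t-test". The Statistical analyses section says "We will use α < 0.05 as the significance level for statistical testing" without naming one or two sides. The form of the within-person correlation is not stated. The paragraph ends by concluding that the planned sample size should be enough for the proposed analyses.

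**The concern.** Because the article prints both the inputs and the results, the results can be checked. On the ordinary reading (two-sided 0.05, equal correlation between any two visits of a person), the printed detectable differences are smaller than the inputs support. The type II error at those effects is then about 27–28% instead of the stated 20%.

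Adherence is a primary outcome, and viral load is the first secondary outcome listed. The closing statement of adequacy rests on these figures, so readers would credit the trial with more sensitivity on both efficacy aims than the stated design gives.

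**Working it through.** **Inputs** (Sample size calculation): n = 55 per arm; m = 3.5 measurements per person on average; correlation ρ = 0.1; alpha 0.05; power 80%; control suppression 85%. **Assumed, because not stated for Aims 2 and 3:** two-sided test and exchangeable correlation.

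**Aim 2**

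1. Variance factor for a person's mean: (1 + (m − 1)ρ)/m = (1 + 2.5 × 0.1)/3.5 = 1.25/3.5 = 0.357.
2. Effective observations per arm: 55/0.357 = 154.
3. Standard error of the difference in SD units: √(2/154) = 0.1140.
4. Detectable difference at 80% power: (1.960 + 0.842) × 0.1140 = **0.319 SD** (0.322 with t quantiles). The plan prints 0.29.
5. Power at 0.29 SD: Φ(0.29/0.1140 − 1.960) = Φ(0.585) = **72.1%**.
6. For scale, 80% power at 0.29 SD would need 2 × (2.802/0.29)² × 0.357 ≈ 66.7, that is 67 per arm.

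**Aim 3**, with the same effective 154 per arm, comparing 85% with 94%

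1. The odds ratio is (0.94/0.06)/(0.85/0.15) = 2.76, which agrees with the printed 2.7 to within rounding of the 9 points.
2. Standard error under the null (pooled proportion 0.895): √(2 × 0.895 × 0.105/154) = 0.0349. Under the alternative: √((0.85 × 0.15 + 0.94 × 0.06)/154) = 0.0346.
3. Power: Φ((0.09 − 1.960 × 0.0349)/0.0346) = Φ(0.62) = **73.3%**. Other common test forms give 70–75%.
4. Detectable difference at 80% power: **9.6 points**, odds ratio about 3.1.

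**Can the printed figures be reproduced by another route?** Each row changes something in the two-sided, exchangeable, m = 3.5, ρ = 0.1 calculation.

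| Route | Aim 2 (SD) | Aim 3 (points; OR) | Power at 0.29 SD / 9 points |
|---|---|---|---|
| As stated, two-sided, exchangeable | 0.319 | 9.6; 3.1 | 72.1% / 73.3% |
| One-sided 0.05 | 0.283 | 8.7; 2.63 | 81.6% / 82.7% |
| Two-sided, ρ = 0 | 0.286 | 8.8; 2.66 | 81.2% / 82.4% |
| Two-sided, all 5 points | 0.283 | 8.7; 2.62 | 82.0% / 83.1% |
| Two-sided, AR(1) at 0.1, 4 points | 0.288 | 8.8; 2.68 | 80.6% / 81.8% |

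The zero-correlation and AR(1) rows round to all three printed values. The one-sided and five-point rows come close, but 0.283 rounds to 0.28. Each row departs from the printed inputs or adds a condition that the text does not give.

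**The case against.** The strongest reply is that sidedness is not stated for Aims 2 and 3 and that their hypotheses are directional. With a one-sided 0.05 test and every printed input unchanged, power at the printed effects exceeds 80% for both aims. Nor does the text name a correlation structure, and an AR(1) form with four points gives the printed values. This much stands: a reader might infer that the figures cannot follow from the stated inputs at all, and the article does not support that. The shortfall is conditional on a two-sided test and exchangeable correlation.

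The reply does not clear the paragraph. No one-sided test is mentioned anywhere, and the only sidedness given, a few lines earlier, is two-sided. The AR(1) match needs 4 points rather than 3.5; interpolating to 3.5 gives about 0.31 SD.

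Two other inferences should be resisted. One is that the authors must have ignored the correlation or the missing visits. Several routes land near 0.29, and the article does not show which was used. The other is that a correlation of 0.1 is itself wrong. No figure in the article contradicts it, and a condensed article may leave its source to the full protocol.

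**Conclusion.** Wrong as written on the natural reading. Assuming a two-sided 0.05 test and exchangeable correlation, the stated inputs give 0.32 SD and 9.6 points, with about 72% and 73% power at the printed 0.29 SD and 9 points. The gap is modest: 0.03 SD and 0.6 points, or 7 to 8 percentage points of power. It disappears if the test was one-sided, but the text would then have to say so.

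A reader might go further and conclude that enrolment must rise or that the trial is seriously underpowered. The documents do not establish either. The finding is that printed inputs and printed results disagree unless an unstated condition is added.

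**What to change.** In Sample size calculation, state for Aims 2 and 3 whether the test is one- or two-sided and which correlation structure was assumed. Then make the figures agree with those choices.

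- If two-sided and exchangeable, restate the detectable differences as 0.32 SD and 9.6 points (odds ratio about 3.1). Alternatively, keep 0.29 SD and 9 points and give the power as about 72% and 73%.
- If another set-up was used, state it and give the inputs that reproduce the figures.
- Tie the closing sentence on sufficiency to the corrected values.

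Optionally, show how the result depends on the correlation, labelled as assumptions: at 0.3 the detectable differences are 0.38 SD and 11.0 points; at 0.5 they are 0.43 SD and 12.1 points (two-sided, exchangeable, 3.5 points).

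The cost is a few lines of text, with no change to enrolment, analysis or conduct. The only downside is that the stated sensitivity looks slightly less favourable.

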### AIM 2. Evaluate the efficacy of the integrated intervention of ISS-SBDOH for monitoring, facilitating and improving adherence to ART

We hypothesize that the ISS-SBDOH arm will have significantly higher mean adherence to ART than the UC arm. GLMM will be used modeling adherence to ART across the contact periods. An arm (ISS-SBDOH or UC) dummy variable will be included in the model to test if the level of adherence is different between the two arms. If the distributions are substantially skewed, we will evaluate categorized clinical cut-off values using generalized estimating equation (GEE) analysis.^95^ For possible non-linear relationships between outcomes and time, we will use generalized additive mixed model (GAMM). The trend of adherence changes before and after 16 weeks will be compared. In addition, we will evaluate group differences in demographics (e.g., gender) and control for these variables in modeling. We also hypothesize that the use of ISS-SBDOH will be associated with lower levels of non-adherence (e.g., fewer single missed doses, a shorter maximum duration of taking no doses) than the UC arm over time. We will make full use of machine learning and data mining methods, including classification and regression trees (CART), random forests, XGBoost, Generalized Additive Models, to identify non-adherence patterns in the data. We will use GLMM/GAMM to model adherence between ISS-SBDOH and UC arm over time to determine if it differs between arms. The GAMM modeling will graphically show the change trend over time. We will also evaluate the distribution of DTEs and their changes over time in the ISS-SBDOH arm. We hypothesize that the differences in adherence between the ISS-SBDOH and the UC arms will be sustained during the 10-week post-intervention period. GLMM/GEE and GAMM will be used to model adherence between the two arms, including parameterization that can distinguish the 16-week trial and 12-week follow-up periods.

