### AIM 3. Evaluate the efficacy of the ISS-SBDOH intervention for improving virologic outcome and reducing high risk sexual activity and STIs

We hypothesize that the participants in the ISS-SBDOH arm will have a low level of viral load and reduced high-risk self-reported sexual activity and frequency of detectable STIs compared to the UC arm. GLMM and GAMM will be used to model viral load of patients and frequency of detectable STIs in the ISS-SBDOH arm and the UC arm across the contact periods (baseline and follow-ups) to evaluate an $$\:arm\times\:time$$ interaction. We also hypothesize that the differences in viral load, and level of high-risk sexual activity and frequency of detectable STIs between the ISS-SBDOH and the UC arms will be sustained during the 12-week post-integrated intervention follow-up period. GLMM/GEE and GAMM will be used to model the viral load, level of high-risk sexual activity, and frequency of detectable STIs between the two arms including parameterization that can distinguish the 16-week intervention phase and 12-week sustainability phase.

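### The sample is called sufficient for all proposed analyses, but durability, STIs and sexual activity were never sized; on the plan's own inputs a follow-up contrast has about 25–54% power

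*Protocol article*

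**What the plan says.** The Sample size calculation section claims a wide scope at the start: "Sample size calculation and power analysis were conducted based on the primary and secondary end points". It then gives three sets of figures, all with 55 per arm:

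- Aim 1: a one-sample binomial approach for acceptability, and a 0.5 SD difference for continuous measures.
- Aim 2: a 0.29 SD difference in outcomes such as adherence, using an average of 3.5 of the 5 data points from baseline to week 16.
- Aim 3: a 9-point difference in viral suppression (85% in the control arm at week 16), with a set-up like that of Aim 2.

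It closes: "Thus, the planned sample size should be sufficient for the proposed analyses".

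The proposed analyses go further. Aim 2 hypothesises that the adherence difference "will be sustained during the 10-week post-intervention period". Aim 3 hypothesises that the differences in viral load, sexual activity and STIs "will be sustained during the 12-week post-integrated intervention follow-up period". For both, the models are to be parameterised so that the intervention phase and the follow-up phase are told apart. Aim 3 also expects "reduced high-risk self-reported sexual activity and frequency of detectable STIs compared to the UC arm". High-risk sexual activity, with STI screening, is listed under Secondary outcomes.

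**The concern.** The closing sentence covers hypotheses for which the section offers no calculation. The adherence and viral suppression calculations use no visit after week 16, and STIs and sexual activity have no assumed rate, effect or power. The durability questions rest on fewer visits than the 3.5 data points behind the 0.29 SD figure, so power for the same effect must be lower there.

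Durability is a stated purpose of the trial. The Study duration section calls the 12-week follow-up long enough to pick up a rapid fading of effects. If power there is near one half or below, a non-significant follow-up contrast cannot separate an effect that has faded from one kept in full. A reader told that the sample is sufficient could easily take such a result as fading, or take a null STI result as absence of effect.

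**Working it through.** **Inputs.** From Sample size calculation: 55 per arm, within-subject correlation ρ = 0.1, 80% power, data availability 3.5/5 = 70%, effects of 0.29 SD and 85% v 94% suppression. From Statistical analyses: "We will use α < 0.05 as the significance level for statistical testing". The only sidedness named is for Aim 1, "a significance level of 0.05 using a two-sided two-sample t-test", so two-sided is used and one-sided is shown beside it. Visits after week 16 are weeks 20 and 28, as stated for viral load (Secondary outcomes) and for SBDOH measures (Primary outcome, item ii). No weeks are given in the text for self-reported adherence, and the schedule figure is not shown. That it follows the same two visits is an assumption.

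**Formulas.** For the mean of m visits with equal correlation, the variance factor is f = [1 + (m − 1)ρ]/m. Then SE = √(2f/55), detectable difference = (1.960 + 0.842) × SE, and power = Φ(0.29/SE − 1.960). A fractional m stands for an average number of available visits.

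**Step 1: the plan's own figure.** With m = 3.5, f = 1.25/3.5 = 0.357 and SE = 0.114. The detectable difference is 0.319 SD, not 0.29, and power at 0.29 SD is 72%. A value close to 0.29 (0.283) appears only if the test is one-sided at 3.5 points, or two-sided with all 5 points present.

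**Step 2: the follow-up contrast, 0.29 SD kept in full.** With m = 2, f = 1.1/2 = 0.55 and SE = √(1.1/55) = 0.1414. Power is Φ(0.29/0.1414 − 1.960) = Φ(0.09) = 54%. With 70% availability of two visits (m = 1.4), f = 1.04/1.4 = 0.743 and SE = 0.1644. Power is Φ(1.764 − 1.960) = 42%.

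| Data in follow-up | Detectable difference (SD, two-sided) | Power, 0.29 SD, two-sided | Power, 0.29 SD, one-sided | Power, 85% v 94%, two-sided |
|---|---|---|---|---|
| Weeks 20 and 28, complete | 0.40 | 54% | 66% | 55% |
| Weeks 20 and 28, 70% available | 0.46 | 42% | 55% | 43% |
| Week 28 only, complete | 0.53 | 33% | 45% | 34% |
| Week 28 only, 70% available | 0.64 | 25% | 36% | 25% |

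The last column is a pooled two-proportion test with effective n = 55/f per arm (for m = 2, 55/0.55 = 100). It carries the 85% control rate forward from week 16, which is an assumption. A higher correlation lowers power: at ρ = 0.5 with two complete visits it is 42%.

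**Step 3: which rows apply.** The documents disagree on the follow-up period. Study duration and Aim 3 give 12 weeks, which after the 16-week intervention ends at week 28. Schedule of events and assessments starts the period after week 20 and adds 10 weeks, which ends at week 30, beyond the last scheduled visit. Aim 2 uses both 10 and 12 weeks. If the period starts after week 20, only week 28 remains.

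**Step 4: the other reading of a sustained effect.** If the test is instead a change in the arm difference between weeks 4–16 and weeks 20–28, the variance factor is (1 − ρ)(1/4 + 1/2) = 0.675 and SE = √(1.35/55) = 0.157. Power to detect complete loss of 0.29 SD is then 46% with all visits present, and 34% at 70% availability.

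**Step 5: STIs and sexual activity.** The documents give nothing to compute from. Purely as assumptions, take control rates per visit of 5% to 30%, relative reductions of 30% to 50%, 3.5 points and ρ = 0.1. Power then runs from about 10% to 89%: 38% for 10% to 5%, 69% for 20% to 10%, and 89% for 30% to 15%.

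**The case against.** The strongest reply on durability is that 0.29 SD is offered as the smallest detectable difference, not the expected effect, so any subset of visits must fall below 80% power at that value. This is true: a real effect of 0.40 SD would have about 81% power with both visits complete. But the section calls 0.29 SD clinically meaningful and uses it to support adequacy, so it is the fair yardstick for a general claim of sufficiency.

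It can also be said that the plan does not fix a separate follow-up contrast, and that a model with one shared arm effect over all visits would have more power. The first part stands. The second does not rescue durability, because Aims 2 and 3 want the two phases distinguished, and a shared effect would not test whether the difference lasts.

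Sizing of secondary questions is often left to a fuller document. Silence alone would therefore be no fault here; the fault is the positive claim.

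Three stronger readings are tempting and are not supported. A reader might infer that a durable effect would usually be missed, but with both visits complete power is 54%, slightly better than even. A reader might infer that the trial is shown to be too small for STIs, but with no stated rate or effect, and repeated measurements planned, power depends wholly on what is assumed. And nowhere do the documents say that a non-significant result will be read as loss of effect; that is a risk, not a stated plan.

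**Conclusion.** The point holds in a limited form. The sufficiency claim is wider than the calculations behind it. For durability, the plan's own inputs give about 42–54% two-sided power if weeks 20 and 28 both count and about 25–33% if only week 28 counts. The one-sided figures reach 66% at most, so no row in the table reaches 80%. This rests on a 0.29 SD effect kept in full, correlation 0.1, a between-arm contrast in the follow-up period, no multiplicity correction, and adherence being collected at the same post-intervention visits as viral load. Partial waning, a higher correlation or the promised multiplicity correction would lower the figures.

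For STIs and sexual activity the finding is only that sufficiency is unsupported.

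The claim is also not secure for end points that were sized. Aim 2 gives 0.319 SD rather than 0.29 on its stated data points with a two-sided test. Aim 1's 0.5 SD has about 74% power with 55 per arm.

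**What to change.** - Remove the blanket closing sentence and limit the claim to end points whose stated power has been verified. For Aims 2 and 3, state whether the test is one- or two-sided and correct the detectable difference to match.
- Reconcile the follow-up definitions (10 v 12 weeks; starting after week 16 or week 20), and state at which visits self-reported adherence is collected.
- State the detectable difference for the follow-up contrast: about 0.40–0.46 SD if weeks 20 and 28 both count, and 0.53–0.64 SD if only week 28 does.
- Report the follow-up, STI and sexual-activity contrasts as estimates with 95% confidence intervals, and state that non-significance there will not be read as loss or absence of effect. STIs can stay within the secondary outcome and need not be relabelled exploratory.

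The cost is a less favourable statement about power and some rewording. No extra patients or visits are needed.
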